#### Analyses

Analyses will focus on understanding implementation and outcome differences between standard and task shifted implementations.

##### Implementation metrics

For the implementation metrics, some data exist at the provider level (families served, fidelity), while others exist at the family level (completion of the program, skill acquisition, satisfaction, perceived cultural relevance). Provider level implementation metrics, including fidelity and adaptations, will be analyzed descriptively because of too few observations for statistical analyses. We will examine mean fidelity and patterns of fidelity over time as adaptations are made. For adaptations, we will describe qualitatively the nature of the adaptations and classify those adaptations conceptually. We will also track adaptations made by SI vs. TS providers by ethnic group. For implementation metrics that exist at the family level (program completion, program satisfaction), we will have either one measurement point (completion of SafeCare, consumer satisfaction, cultural relevance) or two (skill acquisition). For metrics with one measurement time point, analyses of differences between implementation groups will be a simple t-test for continuous variables (satisfaction, cultural relevance) or chi-square analyses for categorical variables (completion). If covariates are needed in the models because of baseline differences, a regression framework will be adopted using linear regression for continuous outcomes and logistic regression for dichotomous outcomes. For skill acquisition, which has two measurement time points, a regression framework will be adopted in which the Time 2 skills are regressed onto Time 1 skills, implementation group, and any relevant covariates.

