### Study aims

There are two primary aims of the study. The first is focused on curriculum adaptations to create culturally appropriate content of a behaviorally-based parenting model, SafeCare©, to be implemented in a community of refugees and immigrants. An adaptation team consisting of model experts, community members, and service providers will adapt SafeCare for Afghan, Burmese, and the Congolese communities. The second aim is focused on an exploration of task shifting by testing two approaches to a community-based SafeCare implementation: (1) implementation as usual via delivery by providers at community-based agencies and (2) a task-shifted approach in which services are delivered by citizens of the community who do not necessarily possess professional backgrounds and education or experience. As previously mentioned, the traditional SafeCare implementation approach is commensurate with Deller’s [36] recommendations for key components pertaining to the training and support of a successful task shifting implementation. Thus, the primary difference in this aim will be about *who* is delivering the program. We will examine implementation metrics including clients served, model fidelity, adaptations, client skill acquisition, and cultural acceptability. We will also examine family outcomes for families served in each method including parenting behavior, parent-child relationship, parenting stress, and child social and emotional health.

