
#### Adaptation process once implementation begins

Once the curriculum is adapted and implementation begins, the adaptation team will continue to meet to discuss implementation and client-driven adaptations. The initial implementation of SafeCare will be carefully monitored in line with Barrera and Castro’s^111^ third and fourth phases, the *preliminary adaptation test* and *adaptation refinement*. The preliminary adaptation test phase typically involves pilot participants. Here, because we expect adaptations to be ongoing and a key question in the study, we will not consider the initial participants pilot participants, but will simply monitor implementation closely as the first participants are enrolled. The goal of the third and fourth phases are to carefully gauge participant reactions to the intervention, discuss any major problems, and make refinements as needed. The adaptation team will continue to meet on a regular basis (biweekly or monthly) depending on the frequency of sessions. Meetings will be coordinated by NSTRC training staff, and as recommended by Barrera and Castro [7] decisions for further adaptations will be made by the team of model experts and cultural experts. If further protocol modifications are needed, we will convene trainees for additional training session.

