#### Analyses

Analyses of data for Aim 1 will be primarily descriptive with the goal of understanding what adaptations were made and to evaluate the process. We will document and categorize adaptations made to the curriculum and implementation process. To assess the process, we will compute means and standard deviations of the quantitative measures collected (initial adaptation needs and the inclusion survey) and conduct qualitative coding of adaptation team members perceptions of the process.

### Aim 2

Aim 2 of this project is to examine SafeCare implementation using two different methods: standard implementation (SI) by community-based agencies and task-shifted (TS) implementation in which community members are trained deliver SafeCare directly to families. The study design is a quasi-experimental design in which we will examine both implementation metrics and family outcomes across the two implementation types.

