#### Referral sources

Referral sources may vary for standard and task-shifted implementation. Recruitment of clients at standard implementation sites will be done primarily from the pool of existing clients already served by those agencies, and referrals received for other services. The resettlement agencies have a range of existing programs and services they offer to families, and families with children in the target age range already being served will be offered SafeCare services. Additional referrals may come from governmental organizations, social service organizations, healthcare providers, and ethnic group organizations.

Recruitment and referrals for services to be delivered by CHWs will be facilitated by the administrative structure of the project. That is, project staff will make connections with community-based referral agencies, advertise the study and services with the help of project stakeholders and community leaders, and direct interested participants to the CHW’s for the service. CHWs are expected to have strong connections to community organizations, social service and health agencies, childcare providers, and ethnic organizations, and those connections should facilitate service referrals. All recruitment efforts will describe the intervention service as a program designed “to build a positive relationship with your child and promote healthy development to be ready for school.”

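### In a non-randomised comparison with different referral routes by arm, three implementation metrics are adjusted only if baseline differences appear, which does not reliably control measured confounding

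*Protocol article*

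**What the plan says.** The opening of Aim 2 describes the design: "The study design is a quasi-experimental design in which we will examine both implementation metrics and family outcomes across the two implementation types". No randomisation or matching is described.

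Under Referral sources the article is open that recruitment differs: "Referral sources may vary for standard and task-shifted implementation". For SI, "Recruitment of clients at standard implementation sites will be done primarily from the pool of existing clients already served by those agencies", with some further outside referrals allowed. For TS, "Recruitment and referrals for services to be delivered by CHWs will be facilitated by the administrative structure of the project", meaning outreach and advertising by project staff, plus the community health workers' own connections.

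The Implementation metrics section then sets three analysis rules or leaves them open:

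- **Completion, satisfaction, cultural relevance** (one time point): a t-test or chi-square between arms. Adjustment is conditional: "If covariates are needed in the models because of baseline differences, a regression framework will be adopted".
- **Skill acquisition** (two time points): always a regression of Time 2 skills on Time 1 skills and arm, with relevant covariates. This has no baseline-difference trigger, but the covariates are not named.
- **Family outcomes** (separate section): a GLMM with time within family, three time points including baseline, and implementation group as the main predictor. No covariate is mentioned.

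The Limitations section names the single module and the lack of a no-intervention group. It does not mention that the SI and TS arms are not randomly formed.

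**The concern.** In a non-randomised comparison a covariate belongs in the model because it plausibly drives both arm membership and outcome. Whether an imbalance happens to be noticed in the sample is the wrong criterion: a moderate true imbalance can go unnoticed and still bias the arm difference. Here the plan itself gives a reason to expect imbalance, since one arm draws mainly on existing resettlement-agency clients and the other on community outreach. Ethnic group, child age, migration history, post-migration difficulties and trauma or mental-health symptoms could all differ by route and be related to whether a family completes the programme and how it rates it.

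At stake is how the SI versus TS difference is read. The Study aims section says "Thus, the primary difference in this aim will be about" who delivers the programme. An arm difference left partly confounded by recruitment route could be credited to the workforce instead.

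**Working it through.** **Inputs.** From the article: 240 families, 120 per arm; detectable difference d = .35 to .45 with attrition up to 20% (Family outcomes section). Assumed, because the article gives no figures: two-sided 5% level; 80% power; a baseline-difference trigger applied as a 5% t-test; confounder imbalance δ between arms in SD units; correlation r (equal to the slope, in SD per SD) between confounder and a continuous outcome; no true arm effect. The SD scale fits satisfaction and cultural relevance directly. Completion is categorical, so there the reasoning carries over but the figures do not.

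**1. The plan's own figure.** Detectable d = (1.960 + 0.842) × √(2/n). With n = 120 per arm this is 0.362; with n = 96 (20% attrition) it is 0.404. The stated range is broadly consistent with 80% power. It cannot be reproduced exactly because level, power and correlation are not given. It serves below only as a yardstick, and it was set for family outcomes, not for these three metrics.

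**2. How often the trigger misses a real imbalance.** Noncentrality = δ × √(120/2); the critical value is 1.970 on 238 df. For δ = 0.25: 0.25 × 7.746 = 1.936, and the chance of a non-significant result is 0.51. For δ = 0.20 it is 0.66; for δ = 0.30 it is 0.36.

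**3. Bias and false-positive rate, one confounder.** Unadjusted bias = δ × r. The other columns come from a simulation of 20,000 runs per row with 120 per arm.

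| δ | r | Unadjusted bias | False positives, unadjusted | Bias, adjust only if p < 0.05 | False positives, adjust only if p < 0.05 |
|---|---|---|---|---|---|
| 0.2 | 0.3 | 0.06 | 7.6% | 0.025 | 5.3% |
| 0.2 | 0.5 | 0.10 | 11.8% | 0.044 | 5.7% |
| 0.3 | 0.5 | 0.15 | 20.7% | 0.030 | 6.1% |
| 0.5 | 0.5 | 0.25 | 49.1% | 0.004 | 4.8% |

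Always adjusting for the confounder gives bias of about 0 and about 5% false positives in every row.

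**4. Why the residual is smaller than δ × r.** When an imbalance is missed, the observed imbalance tends to be small. With standard error √(2/120) = 0.129 and δ = 0.25, the mean observed imbalance given non-significance is about 0.15 SD. Bias when missed is then about 0.15 × 0.5 = 0.075 SD, and averaged over all trials about 0.51 × 0.075 = 0.038 SD.

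**5. Three independent confounders**, each with δ = 0.25 and slope 0.5. Average residual bias is about 3 × 0.038 = 0.115 SD. All three are missed together in about 0.51³ = 13% of trials, and the bias is then about 3 × 0.075 = 0.22 SD. These slopes imply that the three confounders explain 3 × 0.5² = 75% of the outcome variance, so this is a generous illustration.

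**The case against.** The strongest reply is that the rule is narrower and less harmful than it looks.

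- **It does not govern every analysis.** Skill acquisition always carries Time 1 skills and leaves room for covariates without a trigger. A reader might infer that the primary family outcomes will be compared unadjusted. The article does not support that: the Family outcomes section is silent on covariates rather than excluding them, a condensed article commonly leaves such a list to the full plan, and baseline is one of the three time points, so a group-by-time contrast could handle baseline differences in the outcome itself. This stands.
- **No significance test is specified.** The text speaks only of covariates being needed. The 5% test is an assumption used to size the problem. This stands, though an unstated criterion is no safer than a stated one.
- **The trigger catches large imbalances.** At δ = 0.5 almost no bias remains. This stands.
- **A reader might multiply up to 3 × 0.25 × 0.5 = 0.375 SD** and place the bias inside the .35 to .45 range. That requires all three imbalances to be missed, ignores that missed imbalances are smaller than average, and applies a family-outcome yardstick to other endpoints. The figure does not hold.
- **A reader might infer that one arm receives a later curriculum**, since adaptation continues during delivery and "we will not consider the initial participants pilot participants". Nothing in the article staggers the arms, and all providers are trained together.
- **The sentence on who delivers** follows one about shared training and support. It is not a claim that the recruited families are exchangeable. The agencies also serve the wider community beyond their focus on new arrivals, so a sharp contrast in time since arrival is possible but not established.

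None of this justifies making adjustment for known, measured, route-related variables conditional on what the baseline table shows.

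**Conclusion.** The point holds for completion, satisfaction and cultural relevance. Their stated default is an unadjusted comparison in a quasi-experimental design with arm-specific recruitment, and the condition for adjusting does not reliably control measured confounding. Applied as a 5% test with 120 per arm, it misses a 0.25 SD imbalance about half the time.

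The consequence is modest, not fatal. Residual bias is roughly 0.03 to 0.04 SD for one confounder with δ of 0.2 to 0.3 and r = 0.5, and about 0.1 SD in total for three at δ = 0.25 with slopes of 0.5. If no adjustment is made, it is 0.06 to 0.25 SD per confounder over the cases shown. These sizes rest on assumed imbalances and correlations, since the article gives none. To say that the SI versus TS comparison simply stays confounded would go too far as regards measured variables. Unmeasured differences between referral routes do remain under any adjustment rule, and the Limitations section does not say so.

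**What to change.** 1. In the Implementation metrics section, drop the baseline-difference trigger. Always compare completion, satisfaction and cultural relevance by logistic or linear regression on arm and a fixed, pre-named set of baseline variables: ethnic group, child age band (0–12 months or 1–5 years), migration path, and baseline scores on the Post Migration Living Difficulties Scale, the Harvard Trauma Questionnaire and the Hopkins Symptom Checklist.
2. Use the same set as the relevant covariates for skill acquisition and in the family-outcome GLMM. State that the family-outcome arm effect is read as a group-by-time contrast or adjusted for the baseline value.
3. Add to the Limitations that arms are not randomly formed, that SI versus TS compares two delivery systems including their recruitment, and that adjustment cannot remove unmeasured referral-route differences.

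The cost is wording and a few degrees of freedom. No new data collection is needed: the scales and migration path are in the listed assessments, and ethnic group and child age are part of eligibility. Time since arrival is not listed by name, so it can be used only if the migration-path item records it.

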##### Family outcomes

For family outcomes, we will collect data from 240 families (120 SI and 120 TS) at three time points: baseline, post-intervention and four-month follow up (6 months after baseline). With three data points over time, family outcomes will be analyzed in a multilevel context via a GLMM framework with Time nested within Family. The goal is to examine differences in family outcomes between families served by standard and task-shifted implementation, and thus the primary independent variable will be implementation group. The primary outcomes are parent-skills, the parent-child relationship, and parenting-stress. The sample size of 240 was determined via a power analysis and plans to examine differences by implementation type. The sample size provides sufficient power to detect small-to-medium sized differences (*d* = .35–.45) between groups depending on the client attrition (up to 20%) and number of time points.

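### The family-level SI versus TS tests contain no provider or agency level, so they are too liberal if families served by the same provider have correlated outcomes

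*Protocol article*

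**What the plan says.** The Study aims section introduces the SI–TS comparison with "Thus, the primary difference in this aim will be about" who delivers the program. Under Aim 2, SI is delivered by current employees of three resettlement agencies, and TS by community health workers hired by the project.

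The Analyses section under Aim 2 then sets out the comparisons:

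- **Provider-level metrics** (fidelity, adaptations): "will be analyzed descriptively because of too few observations for statistical analyses".
- **Family-level metrics measured once:** "analyses of differences between implementation groups will be a simple t-test for continuous variables", chi-square for completion, and linear or logistic regression if covariates are needed.
- **Skill acquisition:** Time 2 skills regressed on Time 1 skills, implementation group and covariates.
- **Family outcomes:** "family outcomes will be analyzed in a multilevel context via a GLMM framework with Time nested within Family", with implementation group as the primary independent variable.

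On size, "we will collect data from 240 families (120 SI and 120 TS) at three time points". "The sample size of 240 was determined via a power analysis and plans to examine differences by implementation type". The detectable difference is given as d = .35–.45 "between groups depending on the client attrition (up to 20%) and number of time points". No provider count, ICC or design effect is given.

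**The concern.** Provider type is what is being compared, so provider is nested in arm and the SI–TS contrast is a contrast between providers. Families seen by one provider share that person's skill, language and style and, in SI, an agency that decides staffing and how the service is packaged. For skill uptake the provider is also the rater. All of this makes correlation within provider plausible.

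The article recognises the provider level when it declines to test fidelity, then leaves that level out of every family-level test of the same contrast. Ordinary variation between individual providers could then be reported as a difference between implementation methods, which is the Aim 2 question. The covariate option does not help, because fixed provider effects are collinear with arm.

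**Working it through.** **Inputs from the article.** 120 families per arm; attrition up to 20%, leaving 0.8 × 120 = 96 per arm; three assessments, with baseline before any intervention; d = .35–.45.

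**Assumed, because not stated.** Two-sided alpha 0.05; 80% power; k = 3, 6 or 12 providers per arm with equal caseloads m = 120/k (40, 20 or 10 families); provider ICC 0.02, 0.05 or 0.10.

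**1. The plan's own figure.** With independent families, d = √(2/n) × (1.960 + 0.842).

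- n = 120: 0.1291 × 2.802 = 0.36
- n = 96: 0.1443 × 2.802 = 0.40
- At 90% power (1.960 + 1.282): 0.42 and 0.47

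The stated range is compatible with a calculation that has no design effect. It cannot be reproduced strictly, because alpha, power and the within-family correlation are not given.

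**2. Type I error of the planned t-test.** Design effect DE = 1 + (m − 1) × ICC. Actual alpha = 2 × [1 − Φ(1.96/√DE)].

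Example with k = 6 and ICC 0.05: DE = 1 + 19 × 0.05 = 1.95; 1.96/√1.95 = 1.404; alpha = 16%.

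| Providers per arm | ICC 0.02 | ICC 0.05 | ICC 0.10 |
|---|---|---|---|
| 12 (m = 10) | 7% | 10% | 16% |
| 6 (m = 20) | 10% | 16% | 25% |
| 3 (m = 40) | 14% | 25% | 38% |

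Simulated null t-tests on clustered data (5,000 runs per setting) agree within about two percentage points: 9.4%, 15.5% and 26.3% for k = 6, and 14.6%, 25.2% and 39.5% for k = 3. A t-test on provider means stays at about 5%.

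**3. Longitudinal model.** A provider can affect only the two assessments after baseline. Suppose each assessment has unit variance and within-family correlation 0.5 (assumed). Change from baseline then has variance 2 × (1 − 0.5) = 1, so a provider variance of 0.05 acting only after baseline is an ICC of 0.05 for change, and the table applies approximately. Simulation of the arm-by-time test (1,500 null runs per setting, variance components treated as known, normal reference) gave:

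- k = 3, ICC 0.05: 25% with no provider term, 26% with a provider intercept
- k = 6, ICC 0.10: 25% and 24%
- provider differences already present at baseline and stable: 4.4% to 5.5% with no provider term

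A time-constant intercept cancels from change. It therefore neither causes nor repairs inflation of this contrast.

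**4. Detectable effect with clustering.** d = √(2 × DE/n) × 2.802, at ICC 0.05, for a cross-sectional comparison with the normal approximation.

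| Providers per arm | DE, n = 120 | d, n = 120 | DE, n = 96 | d, n = 96 |
|---|---|---|---|---|
| 12 | 1.45 | 0.44 | 1.35 | 0.47 |
| 6 | 1.95 | 0.51 | 1.75 | 0.53 |
| 3 | 2.95 | 0.62 | 2.55 | 0.65 |

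Power for d = 0.45 at n = 120 falls from 94% to 83%, 70% or 53% with 12, 6 or 3 providers per arm. With a t reference on 2k − 2 degrees of freedom it is 79%, 62% or 34%, so the normal approximation flatters the plan.

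**The case against.** The strongest reply is that the size rests on two quantities that appear nowhere in the article. If the provider ICC were zero there would be no inflation, and with 12 providers per arm and ICC 0.01 the actual level is only 6.0%. Large caseloads are themselves an inference from 120 families per arm and the remark about too few provider-level observations. This stands, so the result is conditional and is given as a range.

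A reader might infer that all Aim 2 intervals and p-values are wrong. The article does not support that. Service counts, fidelity and adaptations are not tested inferentially. The table covers the t-tests, and no separate figure was computed for chi-square. For family outcomes the article does not say whether the test is arm or arm-by-time, and stable provider differences leave an arm-by-time test at its nominal level.

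A reader might also assume that adding a provider random intercept settles the matter. Step 3 shows that it does not for change from baseline.

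Finally, the study describes itself as primarily an implementation study, is quasi-experimental, and expects referral sources to differ by arm. A provider term will not remove that confounding. This limits what the contrast can show, but it is no reason to leave its standard errors too small.

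The omission cannot be put down to detail left for an analysis plan, because the article itself names the nesting and the tests.

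**Conclusion.** The point holds conditionally. The stated family-level comparisons omit the level at which the exposure varies, and for any positive provider ICC the single-time-point tests are too liberal. For 3 to 12 providers per arm and ICC 0.02 to 0.10, the t-test's actual type I error is about 7% to 38% instead of 5%. The family-outcome model is affected to a similar degree when provider effects act on change after baseline, under the correlation assumed in step 3. It is not affected when provider differences are stable and the contrast is arm-by-time.

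The stated d = .35–.45 appears to carry no allowance for providers. At ICC 0.05 its upper end is roughly met only with about 12 providers per arm and no attrition. This does not show that the original calculation was wrong on its own terms, since its inputs are not given.

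**What to change.** - **Single-time-point metrics and skill acquisition:** use a linear or logistic mixed model with a provider random effect and small-sample degrees of freedom (Kenward-Roger or Satterthwaite for the linear models), or a t-test on provider means.
- **Family outcomes:** define the contrast as change from baseline. Add a provider random effect that acts on change (provider-by-time or a random provider slope, not an intercept alone), or compare provider-level mean change, again with small-sample degrees of freedom.
- **Further levels:** consider agency and, if group delivery is adopted, delivery group. State how ethnic group is handled, because it may nearly coincide with provider within an arm when providers are few.
- **Power statement:** restate the detectable effect with the number of providers and the assumed ICC, and report the estimated ICC with the results.

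The cost is analysis wording and a revised power statement. No new data collection is evident, provided each family's provider is recorded, which is likely but not stated. The downside is wider intervals and a less favourable detectable effect. With very few providers the comparison may support estimation only.

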#### Assessment of family outcomes

Data will be collected from clients at three assessment points: baseline (prior to any intervention), post-SafeCare (around 6–8 weeks after baseline), and six-months after baseline. Assessments will be interviews conducted by research team members who speak the native language of the participants. Participants will receive a $25 incentive for completing each assessment. Measures to be collecting during the assessment are as follows:
Demographics – standard demographics including current work and living situation, and an assessment of migration path.*Positive Parenting Behaviors* will be assessed using the Parenting Young Children Survey, [59] a 21-item scale assessing three dimensions of parenting behaviors: limit setting, proactive positive parenting, and supporting positive behavior.*Parent-child Relationship and Child Behavioral Health* will be assessed using the attachment subscale of the Devereaux Early Child Assessment [52].*Child health status* will be assessed with the 14-item Functional Status II scale [77].*Parenting Stress* will be assessed via the Parenting Stress Index– short form [3], a 36-item scale designed to measure stressors in parenthood including parental distress, dysfunctional interactions, and stressors related to having a difficult child.*Parent trauma and trauma symptoms* will be assessed with the Harvard Trauma Questionnaire [64] a 17-item scale used to assess both experiences of trauma and trauma symptoms that has been extensively validated in refugee and international populations.*Parent mental health* will be assessed with the Hopkins Symptom Checklist [37], a 25-item scale assessing depression, anxiety, and somatic symptoms.*Social support* will be assessed with 10 items from the Protective Factors Survey [30] which includes concrete and emotional support subscales.*Family Resources* – the 40-item Family Resources Scale – Revised [91] assesses the adequacy of family needs in four domains: basic needs, money, time for self, time for family.*Post-migratory problems –* The Post Migration Living Difficulties Scale (PMLD [84];) is a scale on which respondents rate 24 stressors on the extent to which the issue has caused them problems.*Parent health status and quality of life* will be assessed with the World Health Organization, Quality of Life Scale [95] a 26-items scale assessing physical and mental health, and overall quality of life.

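### The family-outcome analysis names implementation group as its primary term over three visits that include the untreated baseline, with no group-by-time contrast or baseline adjustment stated

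*Protocol article*

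**What the plan says.** Under Aim 2, Analyses, Family outcomes, the protocol article collects data from 120 families per arm "at three time points: baseline, post-intervention and four-month follow up (6 months after baseline"). It then states that "family outcomes will be analyzed in a multilevel context via a GLMM framework with Time nested within Family". The aim is to compare families served by standard and by task-shifted implementation, "thus the primary independent variable will be implementation group". The primary outcomes are parent skills, the parent-child relationship and parenting stress.

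Assessment of family outcomes confirms that the first assessment precedes any intervention. The opening of Aim 2 calls the design quasi-experimental. Referral sources says that recruitment may differ by arm: mainly existing agency clients for standard implementation, and project-led community referral and advertising for the task-shifted arm.

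Elsewhere the article does deal with baseline. Under Implementation metrics, for skill acquisition, "Time 2 skills are regressed onto Time 1 skills, implementation group, and any relevant covariates". The same paragraph allows covariates for baseline differences in the metrics measured once. Family outcomes has no corresponding statement.

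**The concern.** The way SafeCare is delivered cannot affect a measurement taken before delivery starts. If that measurement is an outcome row and the tested effect is group alone, the estimate averages the arm difference over one visit with no possible effect and two visits with one.

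Two consequences follow. A real effect is pulled toward zero by the untreated visit. Any difference between the families the two arms recruit passes into the estimate whole. Randomisation would leave only chance differences at baseline; here the recruitment routes make systematic ones plausible. The group term could then be significant because of who was enrolled, or could miss an effect of the size planned for.

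**Working it through.** **Inputs from the article (Family outcomes).** 120 families per arm; attrition up to 20%, so 120 × 0.8 = 96 per arm; three visits, the first untreated; detectable d of 0.35 to 0.45.

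**Assumed, because the article does not give them.** Two-sided 5% test; 80% power (also 90%); SD 1 at each visit; compound symmetry with within-family correlation r = 0.5 (range 0.3 to 0.7); complete data at the stated n; independent families; δ = 0.40 as the middle of the planned range.

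**Step 1: the article's own figure.** For a comparison at one visit, detectable d = (1.960 + z_power) × √(2/n).
- 80% power: 2.802 × √(2/120) = 0.362; 2.802 × √(2/96) = 0.404.
- 90% power: 0.418 and 0.468.

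This is close to the stated 0.35 to 0.45, although no single set of stated inputs fixes that range.

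**Step 2: what the group term estimates.** Let the arms differ by b at baseline and by b + δ at each follow-up. With equal visit weights the term is [b + (b + δ) + (b + δ)]/3 = b + (2/3)δ. With b = 0, effects of 0.35, 0.40 and 0.45 become 0.233, 0.267 and 0.300. With b = −0.30 and δ = 0.40 the result is −0.30 + 0.267 = −0.033, so the sign reverses.

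**Step 3: power.** SE = √(2v/n) and power = Φ(effect/SE − 1.96). The per-family variances v at r = 0.5 are:
- three-visit mean: (1 + 2r)/3 = 0.667
- follow-up mean minus baseline: (1 + r)/2 + 1 − 2r = 0.75
- follow-up mean adjusted for baseline: (1 + r)/2 − r² = 0.50

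| δ = 0.40, b = 0, r = 0.5 | Estimate | SE, n = 96 | Power | SE, n = 120 | Power |
|---|---|---|---|---|---|
| Group term over three visits | 0.267 | 0.118 | 62% | 0.105 | 72% |
| Difference in change | 0.40 | 0.125 | 89% | 0.112 | 95% |
| Baseline as covariate | 0.40 | 0.102 | 97% | 0.091 | 99% |

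Over r = 0.3 to 0.7, power of the group term falls from 72% to 54% (n = 96) and from 81% to 64% (n = 120). Power of the change contrast rises from 77% to 98.5% and from 86% to 99.6%. At n = 120 and r = 0.5, δ = 0.35 and 0.45 give 60% and 81% for the group term, against 88% and 98% for the change contrast.

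**Step 4: detectable δ at 80% power, r = 0.5.**
- Group term: 2.802 × 0.1054 × 1.5 = 0.443 (n = 120); 2.802 × 0.1179 × 1.5 = 0.495 (n = 96).
- Change contrast: 2.802 × 0.1118 = 0.313; 2.802 × 0.125 = 0.350.

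The stated detectable range therefore depends on which contrast is meant.

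**Step 5: no true effect, stable baseline difference b.** P(significant) = Φ(x − 1.96) + Φ(−x − 1.96), with x = b/SE. At n = 120 and r = 0.5, SE = 0.1054:
- b = 0.1: x = 0.949, 16%
- b = 0.2: x = 1.897, 48%
- b = 0.3: x = 2.846, 81%

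At r = 0.3 these are 19%, 56% and 89%; at r = 0.7 they are 14%, 41% and 74%. A stable b cancels from the change contrast.

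**The case against.** The strongest reply is that the article names a variable, not a coefficient. Calling group the primary independent variable may only mean that it is the factor of interest. The phrase main effect does not appear, the fixed effects are not listed, and a group-by-time term is not excluded. In many longitudinal models group is the factor of interest and is tested through its interaction with time. A condensed article may leave such detail to a fuller plan. Skill acquisition has two measurements, so adjusting the second for the first is natural there and says little about a three-visit model.

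Much of this stands. A reader might infer that the plan definitely tests the group main effect; the text does not establish that. A reader might also take a one-third loss as a general result. It needs an equal effect at both follow-ups and equal visit weights, and with a baseline difference the estimate can be too large, too small or reversed. The documents give no basis for any particular baseline difference, so the percentages in Step 5 are illustrations, not forecasts.

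The reply does not remove the point. The article goes beyond silence: it fixes the data rows, the model and the primary term, and taken together these do not isolate the effect of delivery method. The interaction reading does not rescue the named term either. With baseline as time zero, the group coefficient is then b alone, and the effect lies in a term the article does not mention.

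**Conclusion.** The point holds in conditional form. As worded, the only effect named for inference on the primary family outcomes is group, across data that include an untreated baseline, in a non-randomised comparison. If that term is tested, it carries baseline differences in full and keeps about two thirds of a constant post-baseline effect. At δ = 0.40 and r = 0.5 this costs about 23 to 27 percentage points of power relative to the change contrast (95 − 72 at 120 per arm; 89 − 62 at 96).

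These sizes rest on the assumed significance level, correlation structure, complete data and independent families. The algebra b + (2/3)δ needs only the equal-effect and equal-weight conditions. The documents do not support saying that the authors chose to ignore baseline, or that the analysis will necessarily be biased.

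**What to change.** State in Family outcomes that the primary test is the arm difference after baseline, accounting for baseline. One suitable form is the group-by-time contrast: the arm difference in change from baseline, averaged over the post-intervention and 6-month visits. Estimate baseline means separately by arm, because without randomisation there is no ground for constraining them to be equal.

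Report the model with baseline as a covariate alongside it. In non-randomised arms the two rest on different assumptions and can disagree. Which one leads is a matter of judgement, but it should be fixed before the data are seen. Add that the group main effect from a model holding baseline as an outcome will not be interpreted as the effect of delivery method.

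Restate the detectable difference for the chosen contrast, giving the significance level, power, within-family correlation and attrition assumed. The cost is a few sentences and one recalculation; no new data are needed.
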